### Time of inclusion and randomization

In the Netherlands, most patients with resectable tumours are scheduled to undergo neoadjuvant chemoradiotherapy, which is completed approximately 8 weeks before surgery. Patients will be given information about the trial and will be randomized after neoadjuvant chemoradiotherapy or in the weeks before surgery if neoadjuvant chemoradiotherapy is not indicated.

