### Randomization

Patients will be randomized to the intervention group or the control group with a 1:1 ratio, using a computerized randomization tool (Castor [10]). Patients are stratified according to hospital in order to ensure that other local treatment factors (i.e. postoperative care) are unlikely to interfere with study outcome. Permuted-block randomization with varying block size is used. Allocation and block size are concealed to all investigators. Because of the nature of this trial involving different surgical incisions, blinding treating surgeons and trial participants is unfeasible: A patient will feel whether a cervical incision has been made, and the surgeon knows which operation has been performed. However, a study team member will assess blinded medical reports regarding anastomotic leakage in order to obtain blinded assessment of the primary outcome parameter.

Patients can withdraw from the study at any time. The operating surgeon can decide not to perform a resection during surgery if the tumour is found to be irresectable because of ingrowth into adjacent organs, if perioperative metastases to other organs are found or if resection is unfeasible because of other perioperative events or findings. Modification of the intervention during surgery is justified if the operating surgeon decides he is unable to perform the allocated anastomosis. In this case, follow-up continues according to the trial protocol, and an intention-to-treat analysis will be performed.

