### Statistical analysis

Analyses will be carried out according to the intention-to-treat principle. For dichotomous data, frequencies will be presented, and continuous data will be presented as mean and standard deviation or median and range. The main outcome parameter in the two groups will be compared by calculating both the risk difference and relative risks with their 95 % confidence intervals. An additional per-protocol analysis will be done to evaluate the effectiveness of the intervention with regard to the actual treatment received. Differences in quality of life (as scored by the validated EuroQol 5D, EORTC-QLQ C30 and EORTC-QLQ OG25 questionnaires) will be analysed using a Mann-Whitney test.

Subgroup analysis will be performed on the type and configuration of anastomosis (i.e. side-to-end, side-to-side or end-to-end). Further subgroup analysis will only be carried out in case of significant interaction effects. Potential modification of the effect of each intervention will be evaluated with Poisson analyses.

Patients with open and closed procedures are replaced with new subjects. In the case of missing data, we will perform Poisson regression analyses with a robust covariance matrix estimator to adjust for covariates, since it has been shown that complete case analysis with covariate adjustment and multiple imputation yield similar estimates in the event of outcome data that are missing at random [14]. In addition, we will perform a sensitivity analysis in which a complete case analysis is compared to the multiple imputation analysis, in order to investigate whether multiple imputation would lead to different results.

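### Open-and-close patients are replaced after randomisation, so the set labelled intention-to-treat is, as naturally read, a modified intention-to-treat set

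*Protocol article*

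**What the plan says.** The Statistical analysis section of the protocol article opens with the principle: "Analyses will be carried out according to the intention-to-treat principle". Later in the same section comes the exception: "Patients with open and closed procedures are replaced with new subjects". No modified intention-to-treat population is named. The additional per-protocol analysis concerns the treatment actually received and does not define one.

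The order of events is fixed elsewhere. Under Time of inclusion and randomization, patients "will be randomized after neoadjuvant chemoradiotherapy or in the weeks before surgery", so allocation precedes the operation. Under Randomization, "The operating surgeon can decide not to perform a resection during surgery if the tumour is found to be irresectable". Metastases found at operation are a second ground, and the third applies "if resection is unfeasible because of other perioperative events or findings". The same section says that "blinding treating surgeons and trial participants is unfeasible".

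A different intraoperative departure, in which the surgeon cannot make the allocated anastomosis, is handled explicitly: "In this case, follow-up continues according to the trial protocol, and an intention-to-treat analysis will be performed". That sentence does not clearly extend to patients who have no resection.

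**The concern.** Intention-to-treat means that everyone randomised is analysed in the arm assigned. A patient who is replaced because of something found or decided after allocation is, on the ordinary meaning of the word, no longer in the comparison. The principle and the exception cannot both hold as written.

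Two things are at stake. First, the person deciding knows the arm, and one ground for not resecting is open-ended, so membership of the analysed set could come to depend on the arm. The blinded review of medical reports covers leakage only; it cannot correct who enters the comparison. Second, most secondary endpoints need no anastomosis. Death at 30 and 90 days, organ failure, stay, readmission, quality of life and cost can be recorded for a patient whose operation was abandoned, and leaving these patients out changes what the trial estimates. The Background section faults earlier trials for unexplained exclusions and for lacking intention-to-treat analyses, so this trial should not be open to the same criticism.

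**Working it through.** **1. The plan's own figure.** Inputs from Sample size calculation: p1 = 0.25 (CEA), p2 = 0.10 (IEA), alpha 0.05 (taken as two-sided), power 80%. With pooled variance and p̄ = 0.175:

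n = [1.960·√(2·0.175·0.825) + 0.842·√(0.25·0.75 + 0.10·0.90)]² / 0.15² = 99.5, rounded up to 100 per arm.

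This matches the stated 100 exactly; power at 100 per arm is 80.2%. The figure carries no allowance for loss. It therefore presumes 100 evaluable patients per arm, which fits a plan to substitute patients who have no anastomosis.

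**2. What it costs to keep everyone.** The article gives no open-and-close rate f, so I assume 2%, 5% and 10%, equal in both arms. Recruitment runs until 100 patients per arm have an anastomosis, so 100/(1−f) are randomised per arm. All are analysed, and a patient without an anastomosis counts as no leak, so the rates become 0.25(1−f) and 0.10(1−f).

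| f | Randomised per arm | Rates compared | Power, all randomised |
|---|---|---|---|
| 2% | 102.0 | 24.5% vs 9.8% | 80.0% |
| 5% | 105.3 | 23.75% vs 9.5% | 79.7% |
| 10% | 111.1 | 22.5% vs 9.0% | 79.3% |

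The loss against 80.2% is at most 0.9 points. If instead recruitment stopped at 100 randomised per arm and all were analysed, power would be 79.2%, 77.7% and 74.9%. Continued recruitment is therefore worth having; dropping patients is not needed to protect power.

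**3. Whether either leakage analysis removes bias.** This is a constructed example with no true effect. Leak risk is 17.5% in both arms. Ten per cent of patients are high-risk with 35% leak risk, so the rest have (0.175 − 0.10·0.35)/0.90 = 15.56%. Half of the high-risk patients are abandoned, in the IEA arm only.

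- Exclude them: (0.05·0.35 + 0.90·0.1556)/0.95 = 16.6% against 17.5%, a false benefit of 0.9 points.
- Keep them as no leak: 0.05·0.35 + 0.90·0.1556 + 0.05·0 = 15.75% against 17.5%, a false benefit of 1.75 points.

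If abandonment differs by arm, neither rule is unbiased for leakage, and scoring abandoned patients as no leak does worse here. Both analyses are needed, with the counts by arm beside them.

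**The case against.** The best defence is that a patient without an anastomosis cannot leak, so a leakage analysis limited to anastomosed patients is reasonable. Ingrowth and metastases found at operation contradict the entry condition of a resectable, M0 tumour and are plausibly unrelated to where the anastomosis would have been. The open-ended ground is also limited to cases where "resection is unfeasible because of other perioperative events or findings". The departure most closely tied to allocation, inability to make the assigned anastomosis, stays in under intention-to-treat. Operative technique prescribes the same lymphadenectomy and a gastric tube reconstruction in both arms.

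Much of this stands. It supports a resected-only analysis of leakage, provided that it is named as such. It does not justify the intention-to-treat label, and it does not cover the outcomes that need no anastomosis.

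A reader might go further and infer three things that the documents do not support:

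- **That these patients are certainly removed and not followed.** The text says only that they are replaced. The Follow-up section describes 24 months after surgery for each participant, with no exception. Removal is the natural reading, but it is an inference.
- **That exclusions will differ by arm.** The Discussion calls IEA technically demanding, which makes this conceivable. Nothing shows that the feasibility of resection depends on the arm.
- **That replacement leaves the arms unequal.** The article does not say how a replacement patient is allocated.

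**Conclusion.** The contradiction is in the text. The same section promises intention-to-treat and replaces patients already randomised, on an intraoperative decision by an unblinded surgeon. As naturally read, the analysed set is modified intention-to-treat and is mislabelled. If the sponsor does mean to keep these patients, the sentence still needs correcting, because it does not say so.

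The weight of the point lies in the population label and in the secondary outcomes defined for everyone randomised. It does not lie in a demonstrated bias in leakage: the 0.9-point and 1.75-point figures come from an example built to produce bias, and they compare with a 15-point design difference. The power figures rest on an assumed open-and-close rate of 2% to 10%, equal in both arms, and on the protocol's 25% and 10% leak rates among anastomosed patients.

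**What to change.** Replace the sentence on open-and-close patients with text to this effect:

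- All randomised patients are kept, followed and analysed in their assigned arm for every outcome that does not require an anastomosis.
- Recruitment may continue until 100 patients per arm have an anastomosis, but no randomised patient is removed.
- Leakage is reported in two ways: for all randomised patients, with no anastomosis counted as no leak, and for anastomosed patients only, named as a modified intention-to-treat analysis.
- Open-and-close numbers and reasons are reported by arm.

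The surgeon's criteria for not resecting are left as they are; the change concerns only who is followed and analysed.

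The cost is a few lines of text and follow-up of patients who have already consented: about 2 to 11 per arm at the assumed rates (100/0.98 − 100 to 100/0.90 − 100). Recruitment is no larger than replacement already implies, and the all-randomised leakage analysis gives up less than 1 point of power.

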### Sample size calculation

The incidence of anastomotic leakage requiring reintervention or reoperation (type II or III [6]) after CEA is estimated to be 25 % [2, 13], and this is estimated to be 10 % after IEA [2, 3]. This estimation also corresponds to data from our own database in which data on morbidity after esophageal resection is collected from three of the participating hospitals, and this difference is considered to be clinically relevant. Based on a superiority trial design and taking an alpha of 0.05 and a power of 80 %, 100 patients per treatment arm should be included.

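### The missing-data sensitivity analysis compares two methods that both assume missing at random, so it cannot show whether the leakage result depends on that assumption

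*Protocol article*

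**What the plan says.** All the relevant text is in the Statistical analysis section of the protocol article, in three steps.

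- Method: "In the case of missing data, we will perform Poisson regression analyses with a robust covariance matrix estimator to adjust for covariates".
- Reason, resting on a cited source: "complete case analysis with covariate adjustment and multiple imputation yield similar estimates in the event of outcome data that are missing at random".
- Check: "we will perform a sensitivity analysis in which a complete case analysis is compared to the multiple imputation analysis", with the stated purpose "in order to investigate whether multiple imputation would lead to different results".

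No other missing-data sensitivity analysis is named. The Randomization section allows for loss of data: "Patients can withdraw from the study at any time". No expected rate of missing outcomes is given. Primary leakage status is evaluated 3 months after surgery and quality of life is followed to 24 months (Follow-up section). Quality-of-life scores are to be compared by a Mann-Whitney test.

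**The concern.** A sensitivity analysis for missing data is useful when it varies the assumption that the data cannot check. Here that assumption is that, given the variables in the model, whether an outcome is missing does not depend on the outcome itself. The reason given for the main method already relies on this assumption, and the sensitivity analysis keeps it. If the two results agree, a reader may take the finding to be robust to missing data, when all that has been shown is that two analyses under one assumption agree.

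The stake is the primary comparison. It rests on few events, so a small number of unobserved outcomes, unevenly spread between the arms, could move the confidence interval across zero without the planned check showing it.

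**Working it through.** **1. The plan's own figure.** Inputs from the Sample size calculation section: leakage "after CEA is estimated to be 25" per cent, "this is estimated to be 10 % after IEA", and "taking an alpha of 0.05 and a power of 80 %, 100 patients per treatment arm should be included". With a two-sided test, pooled variance under the null and mean risk 0.175:

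n = [1.960·√(2·0.175·0.825) + 0.842·√(0.25·0.75 + 0.10·0.90)]² / 0.15² = (1.053 + 0.443)² / 0.0225 = 99.5, so 100 per arm. Power at 100 per arm is 80.2%. The stated size reproduces. Expected events are 25 + 10 = 35.

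**2. Why agreement does not test the assumption.** Suppose a fraction m₁ of patients with a leak and m₀ of those without have missing status. The complete-case risk is then expected to be p(1−m₁) / [p(1−m₁) + (1−p)(1−m₀)]. Assume for illustration m₁=30% and m₀=3% in the intrathoracic (IEA) arm, and 5% for both in the cervical (CEA) arm:

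- IEA: 0.10·0.70 / (0.10·0.70 + 0.90·0.97) = 0.070 / 0.943 = 0.074
- CEA: 0.25
- Risk difference 0.176, against a true 0.150

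Multiple imputation that uses only arm and a baseline covariate learns from the same observed patients and inherits the error. A simulation gave these mean risk differences (100 per arm, 400 replicates, 20 imputations, unadjusted complete-case difference, assumed missingness, CEA 5% throughout):

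| IEA missing (leak / no leak) | Full data | Complete case | Multiple imputation |
|---|---|---|---|
| 5% / 5% | 0.141 | 0.142 | 0.142 |
| 30% / 3% | 0.134 | 0.160 | 0.159 |
| 50% / 5% | 0.145 | 0.189 | 0.187 |

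The methods differ by at most 0.002 on average, while both are off by about 0.026 to 0.044 in the last two rows.

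**3. How many missing outcomes would matter.** Assume 5 missing per arm and observed rates close to plan, 24/95 CEA and 10/95 IEA. The test is the pooled z, (p₁−p₂) / √[p̄(1−p̄)(1/n₁+1/n₂)]. The interval is the usual unpooled one for the risk difference, a measure the plan reports.

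| Leaks among missing (CEA, IEA) | CEA v IEA | z | p | Risk difference (95% CI) |
|---|---|---|---|---|
| complete cases | 24/95 v 10/95 | 0.1474/0.0556 = 2.65 | 0.008 | 0.147 (0.040 to 0.254) |
| 0, 3 | 24/100 v 13/100 | 0.11/0.0549 = 2.00 | 0.045 | 0.110 (0.003 to 0.217) |
| 0, 4 | 24/100 v 14/100 | 0.10/0.0555 = 1.80 | 0.071 | 0.100 (−0.008 to 0.208) |
| 0, 5 | 24/100 v 15/100 | 0.09/0.0560 = 1.61 | 0.108 | not needed |
| 1, 4 | 25/100 v 14/100 | 0.11/0.0560 = 1.96 | 0.0496 | 0.110 (0.001 to 0.219) |

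The conclusion changes at 4 of 5 missing IEA leaks with none in CEA. At the planned rates one would expect 5·0.10 = 0.5 leaks among the missing IEA patients and 5·0.25 = 1.25 among the missing CEA patients, so this is an adverse case. With 3 missing per arm at near-planned rates (24/97 v 10/97, p=0.008), even the most adverse allocation, 24/100 v 13/100, leaves p=0.045.

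**The case against.** The case on the other side is substantial, and much of it stands.

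- **Leakage is unlikely to be missing often.** It is not patient-reported. The Primary endpoint section has the treating surgeon and a study team member assess it during treatment, and autopsy is one of the ways to establish it, so death does not by itself erase it. A patient who withdraws after a leak already has the event on record. Data collection and data management provides for checks of the primary outcome against source data. This stands, and it limits the practical weight of the point for the primary endpoint.
- **The numerical examples are adverse.** They need opposite patterns of missingness in the two arms, for which the documents give no evidence. This stands; they show how the planned check behaves and do not forecast the result.
- **The two methods need not agree.** A reader might infer that the comparison must agree and would always reassure. The documents do not support that. The agreement they cite is conditional on missing at random and on covariate adjustment, the imputation model is not fixed, and the complete-case analysis in the check is not said to be adjusted. If imputation uses postoperative variables, results can diverge. Under one assumed scenario (a complication in 80% of patients with a leak and 20% without; IEA missingness 35% with it and 3% without; CEA 5%), the mean risk difference was 0.149 with full data, 0.169 by complete case and about 0.15 by imputation. There the check does useful work. But the missingness is at random once the complication is in the model, so the assumption itself is still not varied.
- **The plan claims nothing false.** It says only that it will see whether imputation changes the result, and the comparison does that. This stands: the weakness is in the choice of check.
- **A separate analysis plan may add more.** It may. The point here is about the sensitivity analysis that the article does fix, not about detail it leaves out.
- **Quality of life.** The missing-data text speaks of Poisson regression, whereas these scores go to a Mann-Whitney test, so it is not clear that the comparison applies to them. One cannot say that the article prescribes it for quality of life.

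**Conclusion.** The point holds in limited form. The one missing-data sensitivity analysis that the article names can show sensitivity to covariates or to the imputation model, but not to departure from missing at random. That follows from the text and needs no assumption about rates.

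Its size does rest on assumptions, because the documents give no missingness rate. With 5 missing per arm at near-planned rates, 4 IEA leaks and no CEA leak among the missing move p from 0.008 to 0.07; 3 missing per arm would not overturn the result. A reader might infer that the primary result is likely to be overturned by missing data. The documents do not support that, since few leakage outcomes should be missing. Missingness linked to illness or death is more likely for the quality-of-life forms collected to 24 months, but no size has been worked out there. This is a worthwhile and cheap improvement to the analysis, not a threat to the design.

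**What to change.** - Keep adjusted complete-case analysis and multiple imputation, and label both as missing-at-random analyses.
- For the primary endpoint, make the sensitivity analysis a tipping-point grid: for each arm, let the number of leaks among patients with missing status run from none to all, recompute the risk difference and relative risk with 95% intervals, report where the conclusion changes, and say whether that combination is plausible given the reasons for missingness. If nothing is missing, the grid is empty and costs nothing.
- For quality of life, add a delta-adjusted analysis, with stated penalties for forms missing in living patients, and do not impute scores after death.

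The cost is a few sentences of analysis wording and a small amount of programming, best settled before unblinded outcome data are seen. Sample size, data collection and trial conduct do not change.

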## Discussion

The use of MIE is increasing worldwide, because it has been shown to reduce postoperative morbidity [15, 16]. A recent worldwide questionnaire study with 478 responders showed that approximately 55 % of surgeons prefer IEA after MIE and that there is a strong trend towards an increased use of IEA instead of CEA for reconstruction of the gastrointestinal tract [17]. However, there is currently no high-quality evidence available that favours IEA over CEA after MIE in terms of anastomotic leakage, other postoperative morbidity, functional results, quality of life or costs. In addition, IEA after MIE is a technically demanding procedure and can be accompanied by considerable postoperative morbidity, probably because of a long learning curve [18, 19]. Without evidence for a benefit of IEA over CEA and in the presence of learning curve associated morbidity, the use of an intrathoracic anastomosis as the standard reconstruction after MIE is questioned.

In theory, both anastomotic locations have possible benefits. Historically, the cervical anastomosis was introduced in order to minimize the disastrous effects of intrathoracic anastomotic leakage [20]. Cervical anastomotic leakage can sometimes be managed by bedside opening [21], although severe intrathoracic complications of cervical leaks have been described [22]. Intrathoracic anastomotic leak used to be associated with a high postoperative mortality of 60 % [21]. However, in the modern era, endoscopic, radiologic and surgical possibilities for treatment of intrathoracic anastomotic leakage have become available, and it now seems a manageable complication [23]. Benefits of the IEA are a lower incidence of anastomotic leakage [2] and possibly a lower incidence of benign strictures requiring dilatation [24–26]. A better healing of the IEA might be explained by resecting the relatively ischemic tip of the gastric tube, providing better vascularized tissue for anastomosis [21, 27]. If IEA proves to be a safe surgical technique, it might be preferred over CEA.

This study is designed to answer the question of whether an IEA or CEA is preferred after MIE. For this trial to succeed, it is essential that all participating centres are surgical experts in the creation of both IEA and CEA in order to avoid the influence of a learning curve, which is the rationale for strict centre invitation and quality control procedures. The ICAN trial will provide important data on anastomotic leakage, other postoperative morbidity, mortality, quality of life, functional results and cost-effectiveness up to 2 years after MIE. The results will aid in clinical decision for the location of the anastomosis and can provide useful information that can be incorporated into future guidelines.

